#### Qualitative variables

2.4.2

The study also explores qualitatively the caregivers’ personal experience with assistance, how and why they experience the level of stress and burden referred in the questionnaire at T0 and T2; the impact of the intervention on caregivers’ burden and older care takers’ perception of the care received; the respondents’ suggestions and opinions regarding the intervention and the online learning platform and chat. Moreover, the body–mind trainers are asked to express their impressions about the caregivers participating in the intervention and the intervention itself (e.g., method, logistics, time), at T1 and T2.

Embodied research methods involve (self) observation including movement-based tasks, somatic journaling, and sensory engagement exercises, allowing participants to express and reflect on their experiences through bodily awareness and gesture. Arts-based methods include creative outputs such as drawings and visual metaphors which serve both as data and as interpretive tools. The combination of quantitative and qualitative methods enables a more comprehensive exploration of how body–mind psycho-educational intervention may contribute to the reduction of burden. This multi-modal approach not only allows for the measurement of participants’ psychological states at a specific point in time, but it also enables the exploration of meaning beyond language, fostering a deeper understanding of participants’ lived realities through aesthetic, emotional, and corporeal dimensions.

The qualitative component invites training participants (the caregivers) and observers to describe their embodied experiences and sensations through metaphors, stories, or drawings (Aita et al., 2003). This approach, grounded in arts-based and embodied research, facilitates the expression of pre-conscious and tacit experiences (Tracy and Redden, 2015; Farquhar and Fitzpatrick, 2019), allowing implicit, non-verbal dimensions of experience to emerge (Tantia, 2021; Leavy, 2020). By moving beyond traditional methods, it supports a direct and holistic engagement with caregiving and care-receiving, enabling participants to convey sensations, emotions, and insights that might otherwise remain unspoken (Spouse, 2000; Stake and Kerr, 1994).

To this purpose, different tools were prepared to be administered over the intervention (as reported in Table 2 and detailed in Appendices 2, 3):(a) *Ad-hoc semi-structured interview with caregivers*. The pre-intervention interview with caregivers includes open-ended questions to comment on the level of stress referred by the interviewees in the questionnaire; questions on the experience of assistance (e.g., negative and positive aspect of caregiving); stressors; available support; feelings of loneliness; awareness of signal of stress coming from the body. The post-intervention interview explores again the burden and depression scores reported by caregivers at the end of the intervention and it also asks: feelings and state of mind at the end of the journey; relationship with the body; relationship with art and expressive activities; experience with the face-to-face intervention, with the e-learning platform and the chat.(b) *The short interview with the older care recipient*. The topic-guide includes questions asking the impressions on the care received, the emotions felt, the prevalent caregiver’s state of mind, the perceived quality of life.(c) *Mid-term short evaluation* is requested from body–mind trainers and caregivers. The interview is administered at T1, after the fourth session of the intervention (that foresees seven face-to-face meetings) to capture any possible aspect that might decrease the efficacy, feasibility and pleasantness of the intervention and, concerning the method, the activities that work better than others.(d) *Observation grid for the observers*. The guidelines for observers allow to capture any change in caregivers’ psycho-body awareness along the intervention sessions; how the caregivers experience enjoyment and usefulness during the intervention; how different artistic ways (movement, creative writing, drawing etc.) adopted throughout the intervention can help caregivers to express themselves and cope with the difficulties of care-giving. In the observation grid, the observers pay attention and note down various qualities of movement (flow, weight, time, space) at all stages of the session, and especially at the beginning and end. They note down their felt sense (Rappaport, 2013) during various stages of the group, and which themes emerged during the sessions. The observers are also asked to describe the whole process with metaphors, single or sequential movements, and they are asked to draw something that reflects what they take away from the session.

Other investigative and monitoring tools, while distinct from the actual study design, were developed to allow for further qualitative and experiential analysis and to facilitate reflection on the DanceCARE experience:(e) *Reporting guide for body–mind trainers*. Across the whole duration of the body–mind part of the educational programme, trainers compile reports of every session. The body–mind trainers are asked to note down their observations on the topics that emerged, group dynamics, and highlights of the training session. The usefulness of the training guide and if they made program adaptations. They are also asked to make notations about the movements of the participants according to the Laban dimension (von Laban and Ullmann, 1971).(f) *Self-observation diary for the caregivers* (training recipients). Caregivers are invited to keep a somatic (self-observation) diary that they can share with the trainers and the group if they wish. Prompts are given to support them in their reflection. These prompts ask about their feelings at the beginning and end of the session, as well as their interactions with their peers and the trainer and the emotional challenges that arose during the session. The caregivers are also asked if they have learned something new (like mindful breathing or communication exercises) and if and how to apply this in their care taking responsibility. Finally, the caregivers are asked which element of the session (movement, interaction, etc.) stayed with them and they would like to repeat. Then, participants are invited to express their experience of the day through a creative medium of their choices such as producing a drawing, writing a short story, or performing a movement sequence that they record on video.

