### Study design

2.1

The main aim of the study is to examine the feasibility of the innovative, blended, and flexible educational program based on DMT and WM methodologies. The second aim is to check if and how the application of key body–mind methodologies contribute to the reduction of burden, depression and isolation of informal and semi-formal caregivers, and at the same time to the increase of the quality of life of older care takers. The study wants to answer the following main research questions “Is the DanceCARE intervention feasible to implement in terms of recruitment, retention, adherence, and acceptability?” and “To what extent and how can the DanceCARE intervention change the perceived burden and depression levels of semi-formal and informal caregivers of older people with long-term care needs?”

Other research questions include whether the intervention also improves the quality of life of the older person receiving care, and whether the blended approach—which involves support through short online videos—is considered helpful and effective by the participants.

To answer these questions, this pilot convergent mixed-method study, chosen in preparation of a future full-scale study, integrates standardized quantitative instruments for measuring perceived levels of burden and depression, with diverse qualitative approaches to capture the complexity of human experience, e.g., interviews, focus-groups and live observations of participants during the body–mind sessions, enriched by art-based and embodied research approach (Hervey, 2000).

These qualitative data will not be limited to verbal accounts; they will also include symbolic and metaphorical expressions emerging from arts-based and embodied practices, which remain grounded within the qualitative paradigm and allow for a process-oriented understanding of participants’ experiences rather than capturing them at a single point in time.

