Quantitative and qualitative datasets will be analyzed separately, and the results will then be merged during the interpretative phase. At this stage, aggregate statistical findings will be integrated with qualitative insights, including both quotations derived from interview transcripts and themes identified through the analysis of arts-based and embodied materials. In line with a convergent mixed-methods design, this integration will involve the systematic comparison and triangulation of quantitative and qualitative results, through strategies such as joint displays and interpretative weaving, to identify points of convergence, complementarity, or divergence (Fetters et al., 2013). This integrative process will enable a more nuanced and comprehensive understanding of participants’ experiences with the intervention, combining verbal accounts with symbolic and embodied expressions.

The study foresees three data collection waves: at the baseline (T0) i.e. 3 months before the start of the training; at mid-time, i.e., after the fourth intervention session (T1), and within 2 weeks from the conclusion of the intervention (T2). The three phases of data collection are described in Figure 1.

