### Sample size, recruitment strategy and inclusion criteria

2.2

The study aims to reach a total of 30 informal (i.e., relatives, friends, neighbors) and semi-formal caregivers (i.e., migrant family care assistant) and 15 older care receivers per country (total 90 caregivers and 45 older adults), without internal stratification considering the very low number of participants. The study is exploratory and is designed to generate in-depth insights into participants’ experiences rather than to test predefined hypotheses. Accordingly, no formal *a priori* power calculation was conducted, because the sample is intended to provide sufficient informational richness (i.e., “information power”) to address the research aims, rather than statistical representativeness. The sample size was decided upon because the few studies on the effects of dance-based interventions have included samples of this scale (Marmeleira et al., 2009), and others based on the use of multiple artistic mediums such as drawing and music involved approximately 20 subjects (McCarthy et al., 2019; Malyn et al., 2020). Furthermore, given that DanceCARE sample is representative for meaning and not statistically representative (Luborsky and Rubinstein, 1995), a study of the statistical power of the sample is not planned (Jones et al., 2003). Feasibility considerations, including recruitment capacity, available resources, and the intensity of the intervention, further informed the target sample size. To account for potential attrition, a dropout rate of approximately 10–15% has been anticipated, and recruitment will be adjusted accordingly where possible. Participant retention will be monitored throughout the study.

Informal and semi-formal caregivers are recruited using the snowballing method (Valerio et al., 2016), through word of mouth and by spreading leaflets in general practitioners’ ambulatories, geriatric hospitals, territorial health and social services, gyms, pharmacies, voluntary and caregivers’ associations, and through social media, i.e., Facebook and piloting organizations’ websites.

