### Outcome variables and research tools

2.4

Employing a mixed-method design, this study will collect data on both quantitative and qualitative outcome variables, explored through proper data collection tools, at three time points (T0–T1–T2).

Table 3 provides an overview of all outcome variables, measures and research tools by target group and data collection waves. In the following two sub-paragraph quantitative and qualitative research tools are deepened.

**Table 3 tab3:** Outcomes variables and tools by target group and data collection time.

Target group	Method	Variables	Tools	Time
Informal and semi-formal caregivers of older adults Older care takers with LTC needs	Quantitative	Variables for the assessment	Common assessment tool	Screening
		Level of stress load	Zarit Burden Interview (ZBI)	T0 and T2
		Dimensions of burden	Caregiver Burden Inventory (CBI)	T0 and T2
		Depression	Beck Depression Inventory (BDI)	T0 and T2
		Satisfaction with the intervention	*Ad hoc* Likert scale-based questions	T1 and T2
	Qualitative	Personal experience with caregiving	*Ad-hoc semi-structured interview*	T0 and T2
		How and why they experience the level of stress and burden referred in the questionnaire		T0 and T2
		Perceived change of stress		T0 and T2
		*Mid-term short evaluation*: Suggestions and opinions regarding the intervention and the online learning platform and chat		T1 and T2
		Self-reflection on the body–mind experience	*Self-observation diary* for the caregivers	longitudinal
	Quantitative	Perceived quality of life	Ad hoc Likert scale-based question	T0 and T2
		Satisfaction with the care received	Yes/no and open-ended questions	T0 and T2
	Qualitative	Perceived care received	Open-ended question	T0 and T2
Body–mind trainers	Qualitative	Reporting on the body–mind sessions	*Reporting guide*	Over the intervention
		*Mid-term short evaluation*: Suggestions for improving the intervention, the online platform use and observed reactions in caregivers	Open-ended question	T1

The tools chosen in the design of this pre-post study to assess depression and psychological distress are validated versions for each country involved in the piloting. They will be sent to participants via online forms for self-administration. In addition, all interviews will be recorded and transcribed initially at the national level and then translated into English to enable a transnational analysis of the data.

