#### Quantitative variables

2.4.1

Feasibility will be evaluated using predefined indicators, including recruitment rate, retention and attrition, adherence to the intervention, and completeness of data collection. Acceptability will be assessed through participant feedback. These parameters will be summarized descriptively to inform the practicality and optimization of the study design.

Concerning the assessment of the impact of the intervention on participants, the primary outcome variables are caregivers’ burden measured using, respectively, the ZBI (Zarit et al., 1987, 1980; Chattat et al., 2011) and the CBI (Novak and Guest, 1989; Valer et al., 2015). The researchers further investigate the aspect of depressive state through the BDI (Beck et al., 1961). These are self-assessment, standardized psychometric instruments, in the form of questionnaires, which can be self-completed by the subjects. It was decided to use two tests to measure caregivers’ burden because the ZBI identifies the consequences of care-giving on the caregiver’s quality of life and psychological and social condition in general, while the CBI delves deeper into the dimensions related to specific individual areas of burden, i.e., objective, psychological, physical, social, and emotional burden.

The ZBI is the most widely used instrument. Originally designed and tested in 1980, it contains 22 questions. Its brevity allows for easy administration and requires the caregiver to respond via a 5-point Likert scale from 0 (never) to 4 (almost always) according to the degree of agreement they have with the individual items. The items investigate how the patient’s disability impacts the quality of life, psychological discomfort, guilt, financial difficulties, shame and social and family difficulties of the caregiver. Consequently, the total score, which is calculated by summing the individual item response scores, is between 0 which corresponds to no care burden, to a maximum of 88 which corresponds to a maximum level of care load. Values between 21 and 40 indicate a light to moderate care burden. Values between 41 and 60 indicate a moderate to severe care burden. Values between 61 and 88 indicate a severe care burden. Scores above 24–26 identify caregivers for whom further investigation and possible support interventions would be indicated (Schreiner et al., 2006).

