#### Participant information and voluntarism

2.6.2

Participants (i.e., informal and semi-formal caregivers and older care takers) will receive detailed information regarding the study’s aims and the structure of the dance-based intervention. This information will be conveyed through written materials (information sheets) and, when requested, through personal consultations with the study’s scientific supervisor ([name]). Both formats will emphasize the voluntary nature of participation, affirming that individuals may withdraw from the study at any point without needing to provide justification and without any negative consequences. The intervention will also be clearly explained to caregivers to ensure transparency.

The nature of the intervention poses no anticipated risks to participants, nor does it involve discomfort or invasion of privacy. Intervention sessions will be facilitated by certified Dance Movement Therapy (DMT) professionals trained in the DanceCARE method. These facilitators possess extensive expertise in body–mind integration practices and are equipped to recognize and appropriately respond to any signs of participant distress. Engagement in the study will not interfere with participants’ ongoing medical treatments or supportive interventions.

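### Caregiver feedback on acceptability is scheduled only after session 4 and at the end, so early leavers have no planned occasion to give it and acceptability is likely, though not certain, to be overstated

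*Protocol article*

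**What the plan says.** Section 2.1 of the protocol article makes feasibility the main aim and asks "Is the DanceCARE intervention feasible to implement in terms of recruitment, retention, adherence, and acceptability". Section 2.4.1 names the source for the last of these four components: "Acceptability will be assessed through participant feedback".

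Table 3 in section 2.4, introduced as an overview of all outcome variables and tools, sets the times. The row "Satisfaction with the intervention" uses ad hoc Likert-type questions at T1 and T2. The caregivers' mid-term evaluation row also carries T1 and T2. Section 2.4.2, item (c), fixes the first point: "The interview is administered at T1, after the fourth session of the intervention". There are seven sessions. Section 2.1 places T2 within two weeks of the end of the programme.

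Section 2.2 plans for a "total 90 caregivers and 45 older adults" and states that "a dropout rate of approximately 10–15% has been anticipated". Section 2.6.2 says that "individuals may withdraw from the study at any point without needing to provide justification". The article describes no feedback or reason item at the time a caregiver stops. In section 2.5, imputation is stated for covariates only.

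**The concern.** Item (c) of section 2.4.2 gives the T1 interview the task of finding whatever might make the programme less effective, less feasible or less pleasant. A caregiver who withdraws during sessions 1 to 3 may know most about that, yet has no scheduled occasion to say so. Retention, attrition and adherence, the neighbouring indicators in section 2.4.1, show how many left but are listed without any item on why.

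Two things are at stake. First, acceptability is a component of the main question, and the answers may be selected towards caregivers whom the programme suited. Second, the pilot is meant to prepare a full-scale study. That study needs to know whether people left because of timing or transport, a care crisis, health, or the activities themselves. This is a matter of data collection: feedback that was never requested cannot be recovered by later analysis.

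**Working it through.** **Inputs from the article**
- Planned caregivers: 30 in each of three countries, 3 × 30 = 90. This reproduces the stated total (section 2.2).
- Anticipated dropout: 10–15%, so 90 × 0.10 = 9 and 90 × 0.15 = 13.5 caregivers (section 2.2).
- Feedback points: after session 4 of 7, and T2 (Table 3; sections 2.1 and 2.4.2).

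**Inputs not in the article, assumed and varied**
- s, the share of responders who are satisfied: 70%, 80% or 90%.
- q, the share of leavers without feedback who would have been satisfied: 0% or 50%.
- The share of dropout that falls before T1: half or all.

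**Who is missed.** A caregiver who leaves after session 4 can already have answered at T1. For acceptability as a whole, the group with no scheduled feedback is those who leave before T1. Write m for that group as a share of all caregivers.

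**Formula.** Acceptability among all caregivers = s(1 − m) + qm. The responder figure is s, so the overstatement is s − [s(1 − m) + qm] = m(s − q).

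**Results (overstatement in percentage points)**

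| Dropout | Share before T1 | m | q | s = 70% | s = 80% | s = 90% |
|---|---|---|---|---|---|---|
| 10% | half | 5% | 50% | 1.0 | 1.5 | 2.0 |
| 10% | half | 5% | 0% | 3.5 | 4.0 | 4.5 |
| 10% | all | 10% | 50% | 2.0 | 3.0 | 4.0 |
| 10% | all | 10% | 0% | 7.0 | 8.0 | 9.0 |
| 15% | half | 7.5% | 50% | 1.5 | 2.25 | 3.0 |
| 15% | half | 7.5% | 0% | 5.25 | 6.0 | 6.75 |
| 15% | all | 15% | 50% | 3.0 | 4.5 | 6.0 |
| 15% | all | 15% | 0% | 10.5 | 12.0 | 13.5 |

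Worked example for the last cell: 0.90 × 0.85 + 0 × 0.15 = 0.765, against a responder figure of 0.90, a difference of 13.5 points. At 10% dropout the same assumptions give 0.90 × 0.90 = 0.81, a difference of 9 points.

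If only half the dropout is early, or if half the leavers were satisfied, every cell lies between 1 and about 7 points. Larger values require both that all dropout is early and that no leaver was satisfied. If leavers were as satisfied as responders (q = s), the overstatement is zero.

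**The case against.** The case on the other side has several parts.

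- **The article is condensed.** It mentions case report forms and appendices that are not shown, and reasons for withdrawal may be recorded there. This has weight, and the point is not that the sponsor has no exit procedure. What stands is that Table 3 is presented as covering all outcomes and tools, and the schedule it gives has no place for a leaver's feedback.
- **T1 and T2 are not limited to attenders.** A reader might infer that only those who stayed are asked, or that anyone who stops never answers. The documents support neither. Section 2.1 says that caregivers are interviewed or asked to respond, without restricting this to those still attending, and section 2.5 invokes intention-to-treat. Anyone who leaves after session 4 can have answered at T1. The gap is therefore confined to caregivers who withdraw before T1, and to the T2 answers of those who withdraw later.
- **The direction is not certain.** A reader might infer that acceptability is bound to be overstated. Section 3.3 expects dropout from worsening health, care crises and changes in the family, not from dislike. If leaving is unrelated to the programme, the bias may be small or absent.
- **Other sources cover the early sessions.** An observer attends every session and notes enjoyment and usefulness, trainers report on each session, and caregivers may keep a diary. These help, but they are not systematic caregiver ratings. The observer records a view of those present, and the diary is shared only if the caregiver wishes. Section 2.4.2 itself sets the trainer reports and the diary apart from the study design proper.
- **Attrition and adherence are reported beside acceptability.** A reader would see that people left, but not why.

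**Conclusion.** The point holds in a limited form. The stated feedback schedule gives caregivers who withdraw before T1 no planned occasion to rate the programme, and no reason for stopping is scheduled. Acceptability is likely, though not certain, to be overstated.

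The size cannot be fixed from the article, because neither the timing nor the reasons for dropout are given. The 1-to-7-point range and the 13.5-point figure both rest on assumed satisfaction rates and on leavers before T1 giving no feedback. They also reduce the planned Likert and open questions to a single satisfied share, a simplification made for the calculation.

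This is a worthwhile and cheap improvement to a collection schedule that bears on the main question. It is neither a contradiction in the plan nor a reason to distrust its other feasibility indicators.

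**What to change.** In section 2.4.1 and Table 3, state three things:

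1. Any caregiver who stops attending, at whatever session, is invited to complete the existing satisfaction items at that time, plus one optional reason item (timing or transport, care crisis, health, distress or dislike of the activities, other). Completion is voluntary, so the right in section 2.6.2 to withdraw without justification is kept.
2. Such a caregiver is still offered the T1 and T2 feedback unless they withdraw from contact.
3. Acceptability is reported with all caregivers who attended at least one session as the denominator, together with the number without feedback.

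As a supplement, show the figure with silent leavers counted as not satisfied, labelled as a worst-case bound. It should not be the main result: some will have left for outside reasons, and treating every exit as dissatisfaction would count attrition a second time.

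The cost is one short form and a few lines of text. Some leavers will not reply, so the gap narrows without closing, and the reported figure may look less favourable.
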